#### Sample Size

A power analysis was performed based on a previous study by Hupin et al [37], and the expected improvement in AHI was estimated to be approximately 8 (SD 10) episodes per hour at the end of the program versus the baseline. The number of participants in each of the two groups (n=25), necessary to achieve such an effect size, was calculated by statistical analysis at 80% statistical power with α=.05.

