## Methods

### Study Design

This study is a 2-arm parallel single-blind randomized controlled trial (registered on ClinicalTrials.gov: NCT04759456), with the per-protocol analysis investigating the effect of the tele-RHB program among 50 male patients with newly diagnosed OSA indicated to CPAP therapy. Patients were recruited from the Sleep Centre of the International Clinical Research Center of St Anne's University Hospital in Brno (FNUSA-ICRC). After providing informed consent, the patients will be randomized to the 12-week tele-RHB program along with CPAP therapy; 25 patients will be randomized to the intervention arm, and 25 will be in the control arm (CPAP therapy alone) in a 1:1 ratio, following the methods described below (Figure 1).

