### Exclusion Criteria

Participants are excluded if they have another type of OSA treatment, chronic corticosteroid therapy or long-term oxygen therapy; they are also excluded if they have at least one of the following health problems: central sleep apnea, chronic obstructive pulmonary disease III or IV, severe pulmonary hypertension, New York Heart Association III or IV, acute coronary syndrome, heart failure, ejection fraction <40%, electrocardiographic-documented heart arrhythmia, severe heart valve disease, cerebrovascular disease, psychiatric disease, and physical disability; in addition, they will be excluded if they do not cooperate during the intervention or do not follow the tele-RHB program and CPAP therapy protocol.

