### Data Analysis

#### Statistical Analysis

TIBCO Statistica (TIBCO Software Inc) will be used for statistical analysis of the obtained data. Statistical analysis will be performed by a person blinded to the experimental conditions. The Shapiro-Wilk test will be used to assess the normality of the data obtained. To compare participants’ baseline and postintervention obtained data within the same group, a paired 2-tailed *t* test will be used for statistical analysis. When comparing the baseline and postintervention data of the participants between both groups, an unpaired *t* test will be used. The level of statistical significance will be set as *P*<.05. The acquired data will be securely collected on an encrypted external hard drive.

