## Discussion

OSA is a severe global problem [6,7,38], negatively affecting the QoL and its various aspects [8,38]. Furthermore, although CPAP therapy is currently considered the gold standard of treatment [38], adherence to its long-term use is low [39]. According to Aardoom et al [40], about 30% to 80% of patients with OSA are nonadherent to their CPAP therapy. However, CPAP adherence and therapy compliance can be improved by a telemedicine-based approach (ie, eHealth) containing regular teleconsultations via video calls [41]. According to Hnatiak et al’s [42] opinion, an additional therapy consisting of the implementation of the tele-RHB program could also improve the severity of OSA or even help with adherence to CPAP therapy. In addition, our comprehensive program, consisting of effective elements of rehabilitation, includes aerobic exercise training [17,18], oropharyngeal training [19], and respiratory muscle training [21], along with recommendations focusing on nutrition, lifestyle, and behavior changes [14-16].

The development of this tele-RHB program for the examined population was based on currently available knowledge. The comprehensive tele-RHB program was designed according to information about effective additional treatment options for OSA mentioned earlier. The study included only middle-aged and older male adults due to the risk of more frequent OSA occurrences in these individuals [3,4]. Thus, significant risk factors for the development of OSA also include middle [4] or older age, smoking [3], and obesity [3,4].

A possible limitation may be the lack of direct physiotherapist supervision during the remotely monitored intervention in a home-based setting. According to Hnatiak et al [42], regular communication of participants with physiotherapists during the intervention should help the standard course of the intervention. Thus, we assume that the completion of this intervention will produce interesting results that will help the further development of additional therapeutic options for OSA.

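### The stated 80% power needs all 25 men per arm in the analysis, but exactly 25 are randomised and the per-protocol analysis removes non-adherers, with no reserve stated

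*Protocol article*

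**What the plan says.** All places are in the protocol article.

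- **Sample Size.** The assumption is that "the expected improvement in AHI was estimated to be approximately 8 (SD 10) episodes per hour at the end of the program versus the baseline". Twenty-five participants per group are described as "necessary to achieve such an effect size, was calculated by statistical analysis at 80% statistical power", with α=.05. No allowance for withdrawal or exclusion is mentioned.
- **Study Design.** The analysis is named as per-protocol, and "25 patients will be randomized to the intervention arm, and 25 will be in the control arm".
- **Randomization.** The list has 6 blocks of 8 and 1 block of 2, that is 6 × 8 + 2 = 50 places.
- **Exclusion Criteria.** Among the reasons for exclusion are lack of cooperation during the intervention and that participants "do not follow the tele-RHB program and CPAP therapy protocol". Both can arise only after randomisation. No adherence threshold is given.
- **Ethical Considerations.** Participants may withdraw at any time.
- **Discussion.** Next to a remark on low adherence in long-term use, the article cites that "about 30% to 80% of patients with OSA are nonadherent to their CPAP therapy", and then says that telemedicine can improve adherence.
- **Measures.** The CPAP devices of all participants are monitored remotely.

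**The concern.** The number randomised equals the number that the power calculation requires in the analysis. The plan nevertheless provides for removing randomised men, and the authors themselves describe adherence as a known difficulty. The sample size section therefore claims a power that the described analysis set reaches only if nobody is excluded and nobody withdraws.

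The intervention arm has two routes to exclusion, CPAP and the rehabilitation programme. The control arm has one. The loss could therefore be larger in one arm as well as larger overall.

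What is at stake is how a null result on AHI is read. A reader would take it as coming from a trial with an 80% chance of detecting the assumed effect, when the analysed number may support appreciably less.

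**Working it through.** **Inputs.** Difference 8, SD 10, so d = 8/10 = 0.8; α = .05; power 80%; 25 per arm (all from Sample Size). Two-sidedness is written only for the within-group test ("a paired 2-tailed" in Statistical Analysis) and is assumed here for the unpaired test. The article words the 8 (SD 10) as end of programme versus baseline. It is used here as the between-arm difference in change, because that reading returns 25.

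**Step 1: reproduce the plan's figure.**

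Normal formula: n per arm = 2 × (1.960 + 0.842)² × 10² / 8² = 24.5, rounded up to 25. Power at 25 is 80.7%.

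Exact two-sided t test: noncentrality = d × √(n/2) = 0.8 × √12.5 = 2.83 on 48 degrees of freedom, power 79.1%. At 26 per arm it is 80.7%.

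Other readings do not explain 25 at 80% power. A one-sided test needs 20 per arm. A paired test needs about 15 men and has 97% power at 25. A one-sided test with 20% loss also gives 20/0.8 = 25, but the article states neither element. So 25 is best read as the number to be analysed, with nothing added for loss.

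**Step 2: power when men are removed equally from both arms.** Noncentrality 0.8 × √(n/2), exact two-sided t, effect unchanged among those who remain. The loss rates are assumptions.

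| Loss | Analysed per arm | Power |
|---|---|---|
| 0% | 25 | 79.1% |
| one man per arm | 24 | 77.4% |
| 10% | 22.5 (22 or 23) | 74.6% (73.6% or 75.6%) |
| 20% | 20 | 69.3% |
| 30% | 17.5 (17 or 18) | 63.2% (61.9% or 64.5%) |

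The 30% row is the lower end of the non-adherence range cited in the Discussion.

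**Step 3: loss in one arm only.** Noncentrality = 0.8 / √(1/n₁ + 1/n₂). With 20 versus 25 analysed, power is 74.1%. With 17 versus 25 it is 70.0%.

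**Step 4: does analysing everyone restore the power?** Keep all 25 per arm but let a share of the intervention arm gain no extra benefit.

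- 20% without benefit: difference 0.8 × 8 = 6.4, noncentrality 0.64 × √12.5 = 2.26, power 60%.
- 30% without benefit: difference 0.7 × 8 = 5.6, noncentrality 0.56 × √12.5 = 1.98, power 49%.

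So an all-randomised analysis does not by itself bring back 80%.

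**The case against.** **The cited range is not a forecast.** A reader might combine the 30–80% non-adherence in the Discussion with the exclusion rule and infer that the trial will have only 63% down to 20% power (17.5 down to 5 men per arm). The arithmetic is right, but the documents do not support the inference. The range is background for patients with OSA in general and stands beside a remark on long-term use, whereas the main comparison here is at 12 weeks. All CPAP devices are monitored remotely, the article expects telemedicine to help adherence, and only men interested in the programme are eligible. No threshold links non-adherence in the literature to exclusion in this trial. This objection stands. The 30% figure can serve as a scenario, but the 80% end cannot be taken as an expectation for this trial.

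**There is no arithmetic error.** This also stands: 25 per arm reproduces. The fault is that the stated power belongs to a larger analysed number than the described analysis set is likely to supply.

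**The effect is worded as a within-group change.** On a literal paired reading, 25 men have 97% power and 17 still have 87%. But that reading does not give 25 as the number needed for 80%, and the trial's hypothesis is a comparison between arms. The between-arm reading remains an assumption and is declared as one.

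**A loss allowance may be in the full protocol, which is not shown.** An omitted detail alone would be no finding. Here, however, the article itself gives 25 as the necessary number, randomises exactly 25, and fixes an analysis that removes randomised men. Those statements need to be brought into line wherever the detail is kept.

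**Conclusion.** The point holds in a limited form. The stated power is attained only if all 25 men per arm are analysed, and then only nominally (80.7% normal, 79.1% exact t). Each exclusion or withdrawal lowers it. Under an assumed 10–20% loss in both arms the shortfall is modest, with power about 75–69%. Under a 30% loss in both arms it is about 63%.

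These figures rest on a two-sided unpaired test, on 8 (SD 10) being the between-arm difference in AHI change, on equal loss in both arms except where stated, and on an unchanged effect among those analysed. The actual loss is unknown, so the conclusion is that the 80% is unsupported for the described analysis set. A specific lower power cannot be asserted.

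**What to change.** 1. In Sample Size, state the expected loss and give the power for the number expected to be analysed, for example 69% at 20 per arm under 20% loss, in place of 80% at 25. State that 8 (SD 10) is the between-arm difference in change, if that is what was meant.
2. In Study Design, make the analysis of all randomised men with a fourth-visit measurement primary, compared as allocated, and keep the per-protocol analysis as supportive. The reason is to avoid selection after randomisation.
3. Move the non-adherence clause out of Exclusion Criteria and into the definition of the per-protocol set, so that it no longer removes randomised men from the primary analysis.
4. Say plainly that the all-randomised analysis does not itself restore 80% power, since non-adherence may dilute the difference: at 6.4 instead of 8, power is about 60% with 25 per arm. The power figures in item 1 assume an undiluted effect and should be labelled so.

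The cost is wording and a change of primary analysis set. No additional recruitment is needed. The downside is a less favourable stated power.

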## Results

Study recruitment began on October 25, 2021, and the estimated study completion date is December 2024. Analyses will be performed to examine whether the combination of the tele-RHB program and CPAP therapy will be more effective in the reduction of OSA severity and improvement of QoL, body composition and circumferences, exercise tolerance, lipid profile, as well as respiratory muscle and lung function, compared to CPAP therapy alone.

## Discussion

OSA is a severe global problem [6,7,38], negatively affecting the QoL and its various aspects [8,38]. Furthermore, although CPAP therapy is currently considered the gold standard of treatment [38], adherence to its long-term use is low [39]. According to Aardoom et al [40], about 30% to 80% of patients with OSA are nonadherent to their CPAP therapy. However, CPAP adherence and therapy compliance can be improved by a telemedicine-based approach (ie, eHealth) containing regular teleconsultations via video calls [41]. According to Hnatiak et al’s [42] opinion, an additional therapy consisting of the implementation of the tele-RHB program could also improve the severity of OSA or even help with adherence to CPAP therapy. In addition, our comprehensive program, consisting of effective elements of rehabilitation, includes aerobic exercise training [17,18], oropharyngeal training [19], and respiratory muscle training [21], along with recommendations focusing on nutrition, lifestyle, and behavior changes [14-16].

The development of this tele-RHB program for the examined population was based on currently available knowledge. The comprehensive tele-RHB program was designed according to information about effective additional treatment options for OSA mentioned earlier. The study included only middle-aged and older male adults due to the risk of more frequent OSA occurrences in these individuals [3,4]. Thus, significant risk factors for the development of OSA also include middle [4] or older age, smoking [3], and obesity [3,4].

A possible limitation may be the lack of direct physiotherapist supervision during the remotely monitored intervention in a home-based setting. According to Hnatiak et al [42], regular communication of participants with physiotherapists during the intervention should help the standard course of the intervention. Thus, we assume that the completion of this intervention will produce interesting results that will help the further development of additional therapeutic options for OSA.

Our study intends to determine whether the completion of a tele-RHB program positively affects OSA in middle-aged and older men, and therefore, provide evidence for a possible recommendation of this tele-RHB program as an effective adjunctive treatment to CPAP therapy in male patients. The study will focus on the expected improvement in OSA severity, QoL, body composition, exercise tolerance, lipid profile, as well as respiratory muscles and lung function, resulting from the completed intervention.

## Appendix

Multimedia Appendix 1 Training brochure—detailed description of the Tele-RHB (comprehensive home-based remotely supervised rehabilitation) program.

## Abbreviations

6MWT: 6-minute walk test
AHI: apnea-hypopnea index
CPAP: continuous positive airway pressure
CRC-UHB: Cardiovascular Rehabilitation Clinic at the University Hospital Brno
ESS: Epworth Sleepiness Scale
FNUSA-ICRC: International Clinical Research Center of St Anne’s University Hospital in Brno
HDL: high-density lipoproteins
LDL: low-density lipoproteins
MEP: maximal expiratory mouth pressure
MIP: maximal inspiratory mouth pressure
OSA: obstructive sleep apnea
PSG: polysomnography
QoL: quality of life
SF-36: Short Form Health Survey-36
SpO_2_: oxygen saturation
Tele-RHB: comprehensive home-based remotely supervised rehabilitation
WHOQOL-BREF: World Health Organization Quality of Life-BREF
